### Stepped wedge trial design

We will use a stepped wedge controlled trial design [33], such that all sites will start with the less intensive implementation strategies (toolkit + IAU) before receiving the more intensive implementation support (toolkit + implementation facilitation) in a staggered fashion (Fig. 1). Stepped wedge designs have their roots in balanced incomplete block designs [34]. A stepped wedge has the advantage of minimizing burden on implementation support personnel as start times are staggered, with all sites ultimately receiving the implementation facilitation strategy. We aim to recruit 16–20 VA Medical Centers (VAMCs) as sites, with about six sites assigned to each of the three waves with start times staggered by 6-month intervals. All sites will start with 3 months in the less-intensive toolkit + IAU condition to allow the collection of baseline data. When each site switches to the more intensive intervention, they will receive 6 months of active implementation facilitation followed by 6 months of step-down.

**Fig. 1 Fig1:**
[figure not shown]
Stepped wedge design and approximate timing of data collection activities. Stepped wedge design (light gray cells denote toolkit + implementation as usual [IAU]; dark gray cells denote implementation facilitation [IF] support)

Our stepped wedge design is novel due to the inclusion of the two types of sites to each wave. This design will accommodate aim 2a above, in that sites within each wave will be assigned to use either the 5-item or 1-item IPV screener. This structure, however, creates novel challenges in assigning sites to study waves. Specifically, we had previously developed a balancing algorithm to minimize the imbalance on key facility-level characteristics between waves in a stepped wedge while retaining some of the benefits of randomization [35, 36]. For the current study, we incorporated our partners’ input in developing a similar algorithm featuring different facility-level variables of contextual relevance to IPV screening program implementation in primary care (Table 1). However, for the current study, we also need to ensure balance between the sites assigned to the 5-item vs. 1-item screener. Thus, our balancing algorithm will identify the least-imbalanced combinations of site assignments across the three study waves and the two screener types on the variables included in Table 1. We will then randomly select from among the 2% least-imbalanced site assignment combinations.

**Table 1 Tab1:** Variables in site assignment balancing algorithm

Construct	Operationalization
1) Total number of non-women’s specific primary care clinics	Total number of mixed gender and separate but share space primary care clinics at the facility (i.e., women’s health primary care model 1 and model 2 clinics)
2) Veterans Integrate Service Network (VISN)	VISN in which the facility is located (regional network)
3) Women Veterans treated in primary care	Number of Women Veterans seen within targeted clinics at the facility
4) Primary care workload	Panel size per primary care provider at the facility
5) Primary care functioning related to mental health	Percentage of primary care patients seen for embedded mental health services with Primary Care Mental Health Integration (PCMHI) clinicians
6) Rurality	Binary; coded as “1” if facility is located within rural county or at least 65% of their patients live in rural areas
7) Facility complexity	VA designation based on several facility variables such as size and availability of certain types of specialty services
8) Emergency Department capacity	Number of Emergency Department visits at the facility
9) Reliance of Women Veterans on VA care	Percent of Women Veterans who get prescriptions at the facility
10) Mental health service capacity	Mental health encounters per unique patient at the facility

### Implementation procedures

#### Toolkit + IAU

All participating VAMCs will initially receive a toolkit, developed by the IPV Assistance Program, to support the uptake of IPV screening programs. The toolkit will include the following tools to encourage the adoption and tailoring of IPV screening programs at individual facilities: (1) VHA’s recommendations for IPV screening programs; (2) VHA’s protocol for screening, response, and referrals; (3) templates notes with screening, response, and disposition; (4) resources to guide clinical response following screening (e.g., IPV brochure, risk assessments, and safety planning tool) and community resources; (5) documentation guidance addressing issues of privacy and safety; and (6) training tools (e.g., PowerPoint slides). In addition, as a condition for participation, all sites must designate a local staff person (e.g., member of the women’s primary aligned care team (PACT)) responsible for launching IPV screening for WVs in primary care at that site. This designated local staff person will fill the internal facilitator role once the more intensive toolkit + implementation facilitation condition begins, as described next.

#### Toolkit + implementation facilitation

Based on our stepped wedge design, all participating VAMCs will be assigned to start receiving implementation facilitation support in wave 1, 2, or 3; this implementation facilitation will be tailored to support either the 5-item or 1-item screener as appropriate (Fig. 1). Implementation facilitation is defined as a multifaceted process of enabling and supporting individuals and groups and has been widely used in primary care settings as an umbrella strategy for overcoming barriers and leveraging strengths to foster implementation of evidence-based interventions and care delivery models [31, 37, 38]. It involves the coordinated efforts of the two types of facilitators, external and internal [39]. The core components of implementation facilitation have been specified and will be assessed during the proposed study [39].

External facilitators are located outside of the local VAMC, implementing the innovation and providing high-level implementation expertise and support. External facilitation will be provided by two Office of Women’s Health Services external facilitators who are clinical experts in IPV and have completed an intensive implementation facilitation training through VHA’s Behavioral Health Quality Enhancement Research Initiative (QUERI) Program’s Implementation Facilitation Training Hub. Operational partners in the VHA IPV Assistance Program provide additional consultation to the Office of Women’s Health Services consultants. Internal facilitators are located within the VAMC and provide boots-on-the-ground knowledge to assist with the implementation. These internal facilitators will collaborate closely with the external facilitators (e.g., through regular email correspondence and a minimum of monthly phone meetings) to support the local implementation of the core components of IPV screening program. Internal facilitators are most often expected to be a member of a women’s health Primary Aligned Care Team (i.e., women’s health physician, nurse, and/or medical director) in collaboration with the facility’s IPV Assistance Program Coordinator. Congress recently funded these coordinator positions nationwide, paving the way for these individuals to play a vital role in supporting the primary care clinics in implementing IPV screening programs.

### Quantitative evaluation of the implementation outcomes

We propose to use RE-AIM as an evaluation framework to guide our qualitative analyses [30]. RE-AIM examines 5 dimensions: reach into the target population, effectiveness of the intervention, adoption by the setting, implementation fidelity, and maintenance (i.e., degree of sustainment over time). Of these, one (effectiveness of the intervention) pertains to clinical effectiveness (aim 2), while the remaining four relate to implementation (aims 1 and 3). Thus, RE-AIM is ideal for structuring the proposed hybrid implementation-effectiveness evaluation. Table 2 describes the specific outcome measures and data sources for each RE-AIM dimension. Given our hybrid type 2 design, we are equally interested in implementation and clinical effectiveness outcomes. For this program evaluation, our primary implementation outcome will be reach (i.e., the proportion of WVs eligible for IPV screening who receive the screening). Our primary clinical effectiveness outcome will be disclosure rates and post-screening psychosocial care use (i.e., the proportion of women with a positive IPV screen who accept a referral and use psychosocial services in the ensuing 2 months).

**Table 2 Tab2:** RE-AIM guides evaluation of the impact and clinical effectiveness of IPV screening programs

RE-AIM dimension (study aim)	Outcome measures	Numerator	Denominator	Data sources
Reach (aim 1): The proportion of eligible WVs receiving IPV screening program.	Proportion of WVs seen in primary care clinics during the last 3 months of each study phase who receive IPV screening	WVs who receive IPV screening as indicated by documentation (templated note, clinical reminder)	WVs seen in primary care clinics who are eligible for IPV screening (WVs seen in clinic with no screen in prior year)	VA Corporate Data Warehouse (CDW): IPV screening status from health factors in templated notes and clinical reminders
Effectiveness (aim 2): The clinical effectiveness of IPV screening programs on disclosure and post-screening psychosocial service use.	a. Proportion of eligible WVs who screen positive for IPV	a. WVs who screen positive for IPV	a. WVs who were screened for IPV	CDW: IPV screening status, responses, and referral disposition (accept or decline referrals) from health factors in note templates and clinical reminders; psychosocial service visits based on clinic stop codes
	b. Proportion of WVs accepting psychosocial service referrals who use such services within 2 months	b. WVs who accepted referral and who use ≥ 1 psychosocial services within 2 months after positive screen	b. WVs who screen positive for IPV and accept a referral	
Adoption (aim 1): The absolute number/proportion of primary care clinics using the IPV screening program.	a. Proportion of primary care clinics completing IPV screening with at least 70% of eligible WVs during evaluation periods	a. Primary care clinics completing IPV screening with at least 70% of eligible WVs during evaluation periods	a. All primary care clinics who saw at least one WV eligible for IPV screening during evaluation periods	CDW: WV patient encounters within primary care clinics. IPV screening status from health factors in note templates and clinical reminders. IPV screening status, resource provision, and referrals offered determined by checkboxes as health factors in note templates and clinical reminders
	b. Proportion of primary care clinics delivering IPV screening program to at least 70% of eligible WVs during evaluation periods, including evidence of resource provision and referral offered for those with positive screens	b. Primary care clinics delivering the IPV screening program to at least 70% of eligible WVs during evaluation periods, including evidence of resource provision and referral offered for those with positive screens	b. All primary care clinics who saw at least one WV eligible for IPV screening during evaluation periods	
Implementation fidelity (aim 1): The extent to which IPV screening programs are conducted as intended by clinics.	Proportion of clinics for whom at least 60% of WVs accepting referrals attend psychosocial services within 2 months of positive screen Note: Additionally assessed via key informant interviews	Primary care clinics for whom at least 60% of WVs accepting referral attend 1 + psychosocial visits within the ensuing 2 months	All primary care clinics who referred at least one screen-positive WV to psychosocial services	CDW: IPV screening status, responses, and referral disposition (accept or decline referrals) from health factors in templated notes and clinical reminders; psychosocial service visits based on clinic stop codes
Maintenance (aims 1 and 3): The degree to which IPV screening programs are sustained over time.	Repeat Reach analysis in last 3 months of study. Note: Implementation strategies and contextual factors impacting maintenance will be assessed via survey and key informant interviews	Same as Reach analysis above, but with data collection occurring 9–12 months after IF ends	Same as Reach analysis above, but with data collection occurring 9–12 months after IF ends	CDW: For repeat of Reach analysis

We will extract relevant administrative and clinical data for all VAMCs from the VA Corporate Data Warehouse (CDW) for all five dimensions of RE-AIM (see Table 1 below for details). The templated note or clinical reminder is required for the study and includes health factors for IPV screening (i.e., disclosure), response (i.e., resources provided), and referrals offered (i.e., accepted or declined IPV Assistance Program-Coordinator referral; accepted or declined psychosocial services referral). Psychosocial care use, and time to first post-screening psychosocial care use, also come from CDW based on clinic stop codes for social work, psychology, psychiatry, primary care mental health integration, drug or alcohol treatment, and housing services.

Our operation partners are interested in testing whether a brief 1-item screener can be as effective as a more comprehensive (but lengthier) 5-item screener a modified Hurt, Insult, Threaten, Scream tool [40], which has been validated for use with the WV population [9, 32]. The tool asks individuals to indicate how often in the past year a current or past partner has done any of the following: “insulted or talked down to you,” “screamed or cursed at you,” “threatened you with harm,” “physically hurt you,” or “pressured or forced you to have sexual activities.” Response options for each item ranges from 1 (never) to 5 (frequently). Endorsement of any item indicates a positive screen. A more efficient screening tool could potentially enhance the uptake of IPV screening programs. However, prior to formal adoption of a 1-item tool, it is critical to evaluate the effectiveness of the tool in eliciting IPV disclosures (sub-aim 2a). The item was developed by a panel of IPV and women’s health clinical experts and researchers and consists of “In the past 12 months, have you experienced insulting, screaming, threatening, hitting, or unwanted sexual activity by a former or current partner?”

We will use repeated measures generalized estimating equations (GEE) [41–43] analyses to address our study aims while controlling for site characteristics (between-site effects) and calendar time, which reflects secular trends (within-site effects). GEE quantifies and apportions the variance in outcomes among relevant factors, thus isolating the change in outcome due to the primary contrast of interest. It extends the traditional general linear model with a continuous outcome (e.g., linear regression) to accommodate binary outcomes for each subject and count outcomes for each site. GEE also accommodates repeated measures (within-subject correlation), random effects (subject), moderate imbalance among independent factors (sites), and various types of missing data. We will include relevant demographic and clinical variables at the patient level (e.g., age, mental health diagnoses, recent psychosocial service use) as covariates. Furthermore, GEE will allow us to explore the results for the patterns of unequal variance, relevant correlation structures, and variance component models to ensure that our results are robust. Our planned sample size will also support the exploration of many site-specific effects by adding site-interaction terms to the model. This method will also allow us to explore the study outcomes using a nested approach (WVs within VAMCs within study conditions). We will use the same GEE-based approach for encompassing each of the five RE-AIM outcome domains included in Table 2 above. Specifically, each primary outcome listed in Table 2 can be expressed as a proportion, and so columns for numerators and denominators are included. Analyses in each of these domains within the GEE framework will consist of logistic regression with random effects.

We will repeat these analyses to compare the clinical effectiveness of the 5-item tool and 1-item tool as well. To evaluate the extent to which IPV screening programs facilitate timely access to psychosocial services, we compare the median number of days to first new psychosocial service visits following a positive screen for women who accepted referrals during and after the IF + toolkit implementation period. In sum, our GEE analyses will allow us to determine the extent to which changes in the quantitative outcome measures described in Table 2 prior to the implementation facilitation differ along two dimensions: (1) based on the changes during and after the implementation period and (2) based on the use of the 5-item vs. 1-item screener.

We will supplement these quantitative data, derived from the CDW, with a 50-item electronic survey to all internal facilitators at pre-facilitation, post-facilitation, and the sustainment phases to assess the use of discrete implementation strategies at each site during each study period. The survey assesses 50 of the 73 strategies described by the Expert Recommendations for Implementing Change (ERIC) study [44], which has shown validity when strategies are assessed via survey [45]. To reduce participant burden, only the 50 strategies most germane to the IPV screening program implementation are queried (i.e., excluded financial incentives as this is irrelevant in VA) and we also inquire about the perceived effectiveness of each strategy on a Likert-type scale. The responses will inform a deeper dive into the use and perceived effectiveness of implementation strategies in subsequent internal facilitator interviews (see Qualitative evaluation of the implementation outcomes and adaptations made to IPV screening programs section).

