### Aims

For this study, we will be comparing two distinct implementation strategies to support the uptake of IPV screening programs. First, all sites will receive a toolkit designed by the IPV Assistance Program, to be distributed to local staff responsible for encouraging IPV screening in primary care (toolkit plus implementation as usual [IAU]). Second, consistent with our stepped wedge design, during the study, each site will be assigned (in a staggered fashion) to cross over to more intensive implementation support in the form of implementation facilitation [31]. Implementation facilitation will entail external Office of Women’s Health Services experts working directly with the local primary care staff at participating sites to encourage IPV screening uptake and will also involve toolkit dissemination (toolkit plus implementation facilitation).

An additional aim of the study will be to compare two IPV screening tools. Specifically, a 5-item screener has been validated to detect probable IPV in primary care settings [9, 32], but feedback from the field to Women's Health Services leadership suggests the length of the 5-item screener may represent an implementation barrier in busy practices. Thus, as a secondary aim, we will compare the utility of the 5-item screener to a 1-item screener. Consistent with the RE-AIM Framework, the proposed research has the following specific aims:
Estimate the degree of reach, adoption, implementation fidelity, and maintenance achieved using two different implementation strategies (toolkit + IAU vs. toolkit + implementation facilitation) (implementation aim)Evaluate the clinical effectiveness of IPV screening programs, as evidenced by disclosure rates and post-screening psychosocial service use (i.e., social work and mental health services uptake) (clinical effectiveness aim)2a. Compare the clinical effectiveness of two IPV screening tools (5-item vs. 1-item screener) in terms of disclosure rates and post-screening psychosocial service useIdentify multi-level barriers to and facilitators of IPV screening program implementation and sustainment

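### Table 2 labels the disclosure outcome per eligible woman but divides it by screened women, so the facilitation contrast is restricted to a group that facilitation is meant to change

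*Protocol article*

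**What the plan says.** All of this is in the protocol article. In Table 2, the Effectiveness row (aim 2) gives outcome a in three cells:

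- Measure: "a. Proportion of eligible WVs who screen positive for IPV"
- Numerator: "a. WVs who screen positive for IPV"
- Denominator: "a. WVs who were screened for IPV"

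The Reach row of the same table shows who counts as eligible: "WVs seen in primary care clinics who are eligible for IPV screening (WVs seen in clinic with no screen in prior year". That group includes women who are then not screened. The text above Table 2 defines reach as "the proportion of WVs eligible for IPV screening who receive the screening".

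The disclosure measure has primary status: "Our primary clinical effectiveness outcome will be disclosure rates and post-screening psychosocial care use". The Aims section and that sentence speak only of disclosure rates and name no denominator. The analysis paragraphs after Table 2 say that the tabulated numerators and denominators form the proportions to be modelled by logistic regression. They also say that changes in these outcomes will be compared "1) based on the changes during and after the implementation period and (2) based on the use of the 5-item vs. 1-item screener".

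**The concern.** The measure cell and the denominator cell describe different populations. Screened women are the numerator of reach, so the two versions of outcome a differ by exactly the quantity that facilitation is intended to move. Each cell carries its own letter a, so this is not an effect of a broken table, and nothing in the text settles which version is meant.

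If the denominator column governs, as the analysis paragraphs imply, the facilitation vs IAU contrast is made only among women who were screened. Being screened follows site assignment and is itself affected by the strategy under test. The women screened under IAU and under facilitation may then differ in kind as well as in number. The article's limitations section itself notes that patient-level factors may influence willingness to be screened.

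Two things are at stake. A primary clinical outcome could show no change, or a fall, while more women with IPV are identified. And with the conflict left open, the denominator could be settled after results are seen, when the two choices may support different conclusions.

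**Working it through.** The article gives no expected disclosure rate. Its only power statement for aim 2 concerns post-screening psychosocial visits and gives no rates, so there is no figure to reproduce. The check is an identity followed by an illustration.

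**Identity.** For the same women in the same window:

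positives/eligible = (screened/eligible) × (positives/screened) = reach × (positives/screened)

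**Inputs**
- From the article (Background): past-year IPV prevalence of 19% among women Veterans in primary care.
- Assumed: reach rises from 10% to 50%, or from 20% to 60%. At low reach, women with IPV are k times as likely to be screened as other women. At high reach this selection disappears (k = 1) unless stated. The screener classifies perfectly.

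**Formulas.** Let q be the chance of screening for a woman without IPV.
- q = reach / (0.19k + 0.81)
- positives/eligible = 0.19 × k × q
- positives/screened = 0.19 × k × q / reach

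**Worked case, k = 2, reach 10%.** q = 0.10 / (0.38 + 0.81) = 0.0840. Positives/eligible = 0.38 × 0.0840 = 3.2%. Positives/screened = 0.38 / 1.19 = 31.9%. At reach 50% with k = 1, positives/screened = 19.0% and positives/eligible = 0.50 × 0.19 = 9.5%.

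**Results**

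| Reach | k at low reach → k at high reach | Per screened (as tabulated) | Per eligible (as labelled) |
|---|---|---|---|
| 10% → 50% | 1 → 1 | 19.0% → 19.0% | 1.9% → 9.5% |
| 10% → 50% | 1.5 → 1 | 26.0% → 19.0% | 2.6% → 9.5% |
| 10% → 50% | 2 → 1 | 31.9% → 19.0% | 3.2% → 9.5% |
| 10% → 50% | 3 → 1 | 41.3% → 19.0% | 4.1% → 9.5% |
| 20% → 60% | 2 → 1 | 31.9% → 19.0% | 6.4% → 11.4% |
| 10% → 50% | 2 → 1.25 | 31.9% → 22.7% | 3.2% → 11.3% |
| 10% → 50% | 0.5 → 1 | 10.5% → 19.0% | 1.0% → 9.5% |

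In every row the per-eligible rate rises. The per-screened rate is flat with no selection, falls when low-reach screening favours women with IPV, and rises when it disfavours them.

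**Check on sub-aim 2a.** Assumed figures: a 1-item tool with 12% positive at 60% reach gives 0.12 × 0.60 = 7.2% per eligible. A 5-item tool with 19% positive at 35% reach gives 0.19 × 0.35 = 6.65%. The tool with the lower yield per woman asked looks better per eligible woman, because reach is mixed into the measure.

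**The case against.** The strongest reply is that the operative definition is not really in doubt. The analysis text points to the numerator and denominator columns, so the outcome is positives per screened woman, and changing one word in the label would remove the contradiction. Reach is already the primary implementation outcome, so the number of women identified can be recovered as the product of two planned outcomes. Patient-level covariates are also planned (age, mental health diagnoses, recent psychosocial service use).

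Part of this stands. Relabelling does resolve the wording, and the covariates may absorb some difference in case mix. But relabelling leaves the facilitation contrast conditioned on a variable that facilitation acts on, and covariates adjust only for what is measured. Recovering a product from two separate analyses is not the same as estimating its effect with a confidence interval.

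A second reply concerns the direction. A reader might infer that the tabulated outcome will show falling disclosure when the programme works. The article does not support that. A fall requires low-reach screening to be enriched for women with IPV, and the article neither states nor excludes this. It describes routine annual screening, with a toolkit from the start and a required templated note or clinical reminder. This objection stands in full against any claim that a fall is expected.

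A third reply concerns sub-aim 2a. A reader might infer that a short tool that raises reach is penalised by the tabulated denominator and that eligible women should replace screened women there too. That does not follow. Without differential selection, the per-screened rate does not depend on reach. The article asks how well the tool elicits disclosure, which is a question about women who were asked. Positives per screened is the natural measure for it, and the 2a arithmetic shows what would be lost by replacing it.

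**Conclusion.** The contradiction is certain: within one table row, a primary clinical outcome has two incompatible denominators that differ by the factor reach. For facilitation vs IAU, following the tabulated denominator restricts the comparison to women selected after site assignment.

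The size of the consequence is conditional. With 19% prevalence, reach rising from 10% to 50% and no selection, the tabulated measure shows no change while five times as many women per eligible woman are identified (9.5 / 1.9 = 5). With twofold selection at low reach, the two versions move in opposite directions. The reach values, the selection factor and perfect classification are assumptions; only the prevalence is in the article.

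It would go too far to say that the randomised comparison as a whole is lost. Reach keeps the full eligible population, and the per-screened rate remains a legitimate yield measure, especially for the screener comparison.

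**What to change.** In Table 2, make the measure and denominator of effectiveness outcome a agree, and state the denominator for each comparison:

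- **Facilitation vs IAU:** analyse screen-positive women per eligible woman, using the Reach denominator and the Reach window. Report positives per screened woman beside it as yield.
- **1-item vs 5-item screener (2a):** keep positives per screened woman, with the label changed to say screened. Report positives per eligible woman and reach alongside.

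The cost is a change of wording in one table row and one additional analysis. The eligible denominator is already extracted for Reach, so no new data source is needed. The drawback is that the per-eligible measure partly reflects reach. It should therefore be read next to both reach and the per-screened yield, so that a gain from screening more women can be told apart from a change in disclosure among those asked.

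### The fidelity measure counts clinics that referred a woman but judges them on women who accepted, so more screening alone can raise the score

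*Protocol article*

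**What the plan says.** All of the relevant text is in the protocol article, section on quantitative evaluation of the implementation outcomes, mainly Table 2.

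- **Fidelity, numerator:** "Primary care clinics for whom at least 60% of WVs accepting referral attend 1 + psychosocial visits within the ensuing 2 months".
- **Fidelity, denominator:** "All primary care clinics who referred at least one screen-positive WV to psychosocial services".
- **Effectiveness b, denominator** (the woman-level attendance measure in the same table): "WVs who screen positive for IPV and accept a referral".
- **Data capture:** the note template records a referral as "accepted or declined psychosocial services referral", so acceptance is a separate field from the offer.
- **Adoption a:** the numerator is "primary care clinics completing IPV screening with at least 70% of eligible WVs during evaluation periods"; the denominator is "All primary care clinics who saw at least one WV eligible for IPV screening during evaluation periods".
- **Status:** "our primary implementation outcome will be reach". Adoption and fidelity are further aim 1 outcomes.

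The same section says that the numerator and denominator columns are given because each outcome is a proportion, to be analysed by logistic regression. So the printed denominators are the ones the models would use. The article does not define what counts as having referred a woman. It also does not say how a clinic with no accepted referral is scored.

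**The concern.** The numerator is conditional on acceptance and the denominator is not. If a referral can be declined, some clinics enter the denominator with no acceptor. Their attendance rate is undefined, they cannot satisfy the 60% rule, and they lower the score for a reason unrelated to attendance.

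This bears on the trial's comparison. Facilitation is meant to raise screening uptake. More screening gives more positives and more referrals per clinic, and so fewer clinics with no acceptor. Fidelity would then look better under facilitation even if women who accept attend at exactly the same rate. A reader would take that as better delivery of the programme.

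**Working it through.** The article states no expected value, sample size or power for fidelity, so there is no figure to reproduce. The check asks how far the printed score moves when only screening changes.

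**Inputs**
- From the article: the 60% cut-off (Table 2), and 19% past-year IPV prevalence (Background), used here as the proportion screening positive.
- Assumed, because the article gives none: 50 eligible women per clinic; every positive woman referred; acceptance *a* = 0.3, 0.5 or 0.7; attendance among acceptors *p* = 0.7; screening rate *s* = 10% or 70%; women independent of each other.

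**Formulas**
1. The chance that an eligible woman is screened, positive and referred is q = 0.19·s: 0.019 at 10% screening and 0.133 at 70%. Expected referrals are 50q = 0.95 and 6.65.
2. A clinic with m ≥ 1 acceptors passes with probability P(X ≥ r), where X ~ Binomial(m, p) and r is the smallest count with r/m ≥ 0.60.
3. Among clinics with at least one referral, the share with no acceptor is z = [(1 − qa)^50 − (1 − q)^50] / [1 − (1 − q)^50].
4. The matched score M averages step 2 over clinics with at least one acceptor. The printed score is M·(1 − z), because clinics without an acceptor count as not passing.

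Worked case, a = 0.3, s = 10%: z = (0.751 − 0.383)/0.617 = 0.597; M = 0.675; printed score = 0.675 × 0.403 = 0.272.

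**Results at 70% attendance, screening 10% → 70%**

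| Acceptance | Share with no acceptor | Printed score | Matched score |
|---|---|---|---|
| 30% | 0.60 → 0.13 | 0.27 → 0.57 | 0.68 → 0.65 |
| 50% | 0.38 → 0.03 | 0.41 → 0.67 | 0.66 → 0.69 |
| 70% | 0.21 → 0.01 | 0.52 → 0.71 | 0.65 → 0.72 |

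The printed score gains 30, 26 and 19 points (differences of the rounded values). The matched score changes by −2, +2 and +6 points (before rounding).

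**Other attendance rates.** The same formulas over the three acceptance rates give printed gains of 3 to 16 points at p = 0.5, 11 to 22 at p = 0.6 and 25 to 36 at p = 0.8. Matched changes run from −7 to +9 points over these three attendance rates. The artefact is therefore smaller when attendance is low or acceptance is high. A modest residual remains after matching, because a hard cut-off is not linear in caseload.

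**Secondary check: noise of the cut-offs.** With true attendance exactly 60%, the pass probability for 1 to 5 acceptors is 0.60, 0.36, 0.65, 0.48 and 0.68. With true screening exactly 70%, the adoption probability for 1 to 4 eligible women is 0.70, 0.49, 0.34 and 0.65. Few acceptors is plausible: the clinic above, at 70% screening and 30% acceptance, expects 6.65 × 0.3 = 2.0.

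**The case against.** The strongest reply is that the mismatch hangs on one undefined word. Where the article means an offer, it says so (Adoption b and the template description), and the Background describes referrals as made when patients want them. A referral in the fidelity row may therefore mean an accepted one, in which case the two sides agree. Nor does any passage say that a clinic with no acceptor is scored as failing. Both points stand. They turn the defect into an ambiguity without removing it: the row uses a different term from its own numerator and from Effectiveness b, and the clarification needed is the same one-line edit.

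It can also be said that the size rests on assumed inputs, that reach is the named primary implementation outcome, and that interviews supplement fidelity. All of this is true and limits the weight of the point.

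A reader might infer three stronger claims, and the article supports none of them.
- *Adoption is confounded in the same way.* Its denominator rests on eligible women seen, which facilitation does not aim to increase. Because eligibility requires no screen in the prior year, earlier screening could even reduce it.
- *The scores reflect caseload instead of performance.* They reflect both. With 10 acceptors, the pass probability goes from 0.38 at 50% attendance to 0.85 at 70%.
- *A fixed minimum caseload is required.* Any chosen number would be arbitrary, and a minimum number of acceptors would make inclusion depend on a count that facilitation may change.

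**Conclusion.** The fidelity denominator does not match its numerator as printed and should be corrected. Under the assumptions shown, with attendance at 70%, a rise in screening from 10% to 70% produces an apparent fidelity gain of 19 to 30 points with no change in attendance. A matched denominator reduces this to about 6 points at most. The true size in this trial cannot be fixed, because clinic caseloads and acceptance rates are not given. If a referral was meant as an accepted referral, there is no artefact and only the wording needs changing.

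The 60% and 70% cut-offs are noisy in clinics with one or two women. That is a caution for interpretation and does not show a biased comparison. The named primary outcomes are not affected.

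**What to change.** In the fidelity row of Table 2, change the denominator to all primary care clinics with at least one screen-positive woman who accepted a psychosocial services referral. This matches the fidelity numerator and Effectiveness b. The template already records acceptance, so no new data are needed.

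The cost is small: clinics with no accepted referral leave this measure. Reporting how many there are in each condition would keep that visible.

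Keep the clinic-level cut-offs if wanted, but read adoption beside the woman-level Reach result and fidelity beside the woman-level Effectiveness b result. Both are already in Table 2.
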